**Recruitment**

The study will be conducted by the University of South China (the central research headquarters). However, there are three centers participating in this project: the First Affiliated Hospital, Hengyang Medical School, University of South China; the First Affiliated Hospital of Hunan University of Traditional Chinese Medicine; and the Affiliated Changsha Central Hospital, Hengyang Medical School, University of South China. Participants will be publicly recruited according to three major strategies. The first strategy is to recruit participants from the three aforementioned hospitals. The second strategy is to print recruitment posters and distribute them across major health institutions and frequented public places to recruit potentially eligible research participants. The third strategy is to publish online advertisements introducing our study and recruiting volunteer participants.

**Inclusion criteria**

Eligible participants must meet all of the criteria below to be considered for this study:

1. Diagnosed with PDMM according to the International Classification of Diseases criteria (ICD-10-I63; Code: 902)

(2) Aged 16–35 years.

(3) Regular menstrual cycles (defined as 28-day cycles ± 7 days) for 4–7 menstrual days.

(4) Detailed contact information provided, with no short-term migration and ability to attend follow-up visits.

(5) Received no treatments within the preceding month, including acupuncture, NSAIDs, anti-inflammatory drugs, and analgesics.

(6) Willing to cooperate with the treatment procedures, medical examination, and efficacy evaluations, and must agree to not participate in other clinical experiments during the study period.

(7) Provision of written informed consent prior to participation.

(8) VAS score (i.e., the primary study endpoint described above) for three consecutive menstrual cycles ≥ 4 cm.

**Exclusion criteria**

Participants were excluded for any one of the following:

(1) Diagnosis of secondary dysmenorrhea (i.e., dysmenorrhea caused by uterine fibroids, adenomyosis, endometriosis, pelvic inflammation, internal foreign bodies, ovarian lesions, or other organic lesions).

(2) Irregular menstrual periods

(3) History of thrombosis, embolism, cerebrovascular disease, coronary artery disease, or high risk for thrombosis.

(4) Mental illness or cognitive impairment preventing comprehension of scale evaluation content.

(5) History of complications, depression, or antidepressant medication use.

(6) Severe heart, lung, liver, kidney, blood, immune, or endocrine system diseases.

(7) Hematopoietic diseases, acquired immunodeficiency syndrome, tuberculosis, hepatitis, or miscellaneous infectious diseases (as differentiated from the specific infections defined above).

(8) Malignancy, history of malignancy, or malignancy findings.

(9) Pregnancy, planned pregnancy, or lactation within 1 year.

(10) History of jaundice or herpes during pregnancy.

(11) Participation in other clinical studies within 4 weeks before provision of informed consent.

(12) Use of any of the following drugs within 4 weeks before provision of informed consent: gonadotropin-releasing hormone analogues or testosterone derivatives, hormone preparations containing mainly progesterone or estrogen, estrogen antagonists or aromatase inhibitors, and ongoing treatment for other gynecological diseases.

(13) Metal allergy or severe needle phobia such that electroacupuncture treatment cannot be tolerated.

(14)Skin rupture from needle, scars, or cardiac pacemaker.

(15) Other lesions or conditions deemed inappropriate or too complicated according to the judgment of the researchers, such as frequently changing work environment or unstable living conditions, which easily cause loss to follow-up.

**How will participants be identified and initially contacted including screening processes?**

The snowballing process and public advertisement can identify potential participants. People interested in participating in the study will be encouraged to contact the research team via email for an eligibility check. We will send online screening checklist, including Various scales,to assess their suitability for participation.

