**Study design:**

We propose to conduct a multicenter, randomized, participant-blinded, sham-controlled clinical trial evaluating the effects of EA on PDMM in which participants will be publicly recruited. All centers must screen cases in strict accordance with the specified diagnostic, inclusion, and exclusion criteria, as specified below. A total of 336 participants with PDMM will be randomly assigned to two groups. The treatment group (n = 168) will receive EA, and the control group will receive SA (n = 168). The study will include the participants, implementing efficacy evaluators, and a data statistician. With regard to SA, the enrolled participants will be blinded and evaluated blindly after the last treatment.

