Participants in the sham acupuncture group will receive sham electric acupuncture with false (sham) acupuncture points. The sham SP6 point is located 2 cun (approximately 40 mm) above taixi (KD3, midway between the spleen and kidney meridians [Fig 2A]). The sham CV4 point is located between the qihai (CV6) and yinjiao (CV7) levels, 3 cun lateral to the midline (Fig 2B). SA acupuncture needles will be inserted into the surface of skin (2–3 mm). There was no acupuncture technique whatever and have no de qi. The same electrode placements and other treatment settings will be used as in the EA group. However, the internal power cord will be cut off without any actual current output. Throughout the trial, participants will be treated individually with procedures in place to prevent communication between participants. To test for the blinding effect of the participants, all participants will be asked to guess whether they received an EA or a SA within 5 minutes of one session at week 12.

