
The randomization scheme and parameters set during scheme generation are collectively known as the blind background. This study follows a first-level blind design, in which the primary randomized number corresponds to the actual treatment group. The random coding table is generated by the statistical unit, and the blind bottom will be sealed separately and delivered to the responsible clinical trial unit at The First Affiliated Hospital, Department of Chinese Medicine, Hengyang Medical School, University of South China.

The central randomization system designates strict personnel authority. More specifically, no one other than the highest administrator is allowed to view the random scheme within the system, thereby ensuring a completely random distribution and effectively eliminating human interference and error.

The investigator will not perform emergency unblinding unless grouping information is required to medically treat the patient.

In this trial, the emergency unblinding process involves electronic emergency letters. When the investigator believes that the grouping information is required for the treatment of serious adverse events, emergency unblinding can be achieved through the LNKMED Interactive Web Randomization System. Meanwhile, the researcher will record the relevant data in detail, including the time of unblinding, cause, trial treatment, treatment, etc. Once the electronic emergency envelope is opened, the participant will be treated as a shedding case.

**Please provide a response to any ethical issues and concerns raised by the recruitment process such as the relationship between researchers and participants, risks associated with recruitment strategy, and the nature of the population being examined.**

There is no single correct approach, but a balanced recruitment approach will be employed (e.g., use snowballing as well as public advertisement). Recruitment of participants should be viewed as part of the research protocol and should require appropriate informed consent of the already-enrolled participant. Investigators should inform prospective participants why they are being contacted, how information about them was obtained, and what will happen to that information if they decide not to participate.

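### Snowball recruitment works against the protocol's own measures to keep participants from communicating and puts blinding of a self-rated primary outcome at risk

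*Protocol*

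**What the plan says.** The protocol's section on identifying and first contacting participants states: "The snowballing process and public advertisement can identify potential participants". The response to ethical concerns, under the section on formal recruitment, gives as its example of a balanced approach "use snowballing as well as public advertisement". It adds that recruitment "should require appropriate informed consent of the already-enrolled participant", which points to referral by women already in the trial.

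Two other places bear on this. The Recruitment section says "Participants will be publicly recruited according to three major strategies" and then names the three hospitals, posters and online advertisements; referral is not among them. The sham-group text under Intervention and exposure says: "Throughout the trial, participants will be treated individually with procedures in place to prevent communication between participants". The procedures are not described beyond individual treatment. On blinding, the Study design section says "With regard to SA, the enrolled participants will be blinded and evaluated blindly after the last treatment".

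**The concern.** Snowballing brings in women who know someone in the trial. Treating each woman alone limits contact in the clinic, but it does not reach two women who already talk to each other. One recruitment route therefore creates the contact that the intervention section is meant to prevent.

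At stake is the main protection of the primary outcome. Pain on the VAS is placed on the scale by the woman herself. If a sham participant hears that an acquaintance felt deep needling and current, she may infer her arm and rate her pain accordingly. The expected direction is a larger difference in favour of electroacupuncture, produced by expectation rather than treatment.

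**Working it through.** The protocol states no figure on this point, so there is none to reproduce. The check sets the sections side by side, then gives the one probability that follows from the design, then an illustration under stated assumptions.

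**1. Can the arms be told apart by comparing notes?** From Intervention and exposure:

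| Feature | Electroacupuncture | Sham |
| --- | --- | --- |
| Insertion depth | about 16–30 mm | 2–3 mm |
| Manipulation and de qi | yes | none |
| Current | 1–5 mA, slight movement of the skin | none |
| Points | SP6, CV4 | other sites |

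A woman treated alone has nothing to compare with; two acquaintances do. There are 21 sessions over three cycles, so the opportunity is repeated.

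**2. How often would acquainted women be in different arms?** Inputs: 336 women, 168 per group, individual 1:1 allocation. Ignoring centre and blocks, a linked group of k women contains both arms with probability 1 − 2·C(168,k)/C(336,k). For k = 2 this equals 168/335 = 0.50. For k = 3, 4 and 5 it is 0.75, 0.88 and 0.94.

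**3. Illustration of bias.** Let f be the share of women in linked pairs and b the mean shift in the electroacupuncture-minus-sham VAS contrast among women in split pairs. The protocol gives neither.

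Bias = f × (168/335) × b

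- f = 0.10, b = 0.5 cm: 0.10 × 0.5015 × 0.5 = 0.025 cm
- f = 0.20, b = 1.0 cm: 0.20 × 0.5015 × 1.0 = 0.10 cm
- f = 0.50, b = 1.0 cm: 0.50 × 0.5015 × 1.0 = 0.25 cm
- f = 0.50, b = 1.5 cm: 0.50 × 0.5015 × 1.5 = 0.376 cm

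These values let every split pair overlap in time, compare sessions and infer their arms. If only some do, the bias shrinks in proportion.

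**4. What such a bias does to the test.** With no true effect, 168 per arm and an assumed SD of 2 cm, SE = 2 × √(2/168) = 0.218 cm. The two-sided 5% error becomes 1 − Φ(1.96 − bias/SE) + Φ(−1.96 − bias/SE):

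| Bias | SD 1.5 cm | SD 2 cm | SD 2.5 cm |
| --- | --- | --- | --- |
| 0.05 cm | 6.1% | 5.6% | 5.4% |
| 0.10 cm | 9.4% | 7.4% | 6.6% |
| 0.25 cm | 33% | 21% | 15% |

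The SD is also not in the protocol. The tables show what would matter, not what will happen.

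**The case against.** The strongest reply is that the text does not establish a failure. Snowballing is described permissively: it is something that can identify women, and it appears as an example. The three listed strategies are called major, which leaves room for minor ones. The document also carries text that seems to belong to other projects: a laser-type therapy for office workers in the PICOs, a school of nursing in the data-collection section, and feasibility rates as primary outcome in the second statistical section. The snowballing lines may be similar remnants. The procedures against communication are unspecified and could include an instruction not to talk; consent pages are not in the available copy. Finally, every participant guesses her arm at week 12.

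Much of this stands, and it limits the strength of the claim. It does not remove it. If the lines are remnants, they should come out; if they are intended, no section says how contact outside the clinic is handled. A guess at week 12 may detect lost blinding, but it comes at the end of treatment, cannot prevent the loss and cannot trace it to referral.

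A reader might also infer that outcomes of linked women are no longer independent and that the standard error is therefore wrong. With individual allocation, correlation within pairs has little net effect on the arm contrast, and in split pairs ignoring it is conservative. That point carries little weight here.

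**Conclusion.** The point holds as a risk and an inconsistency. Snowballing, read as referral through enrolled women, undermines the stated measures against communication, endangers participant blinding of a self-rated outcome, and is missing from the three listed strategies. The 0.50 chance that a linked pair is split follows from 1:1 allocation. The bias of about 0.03–0.38 cm rests entirely on assumed referral shares and shifts, so its true size is unknown.

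Two stronger readings are not supported. One is that snowballing defeats blinding or breaks a ban on communication: the text describes preventive procedures, not a ban, and does not say who would be referred or whether they would compare sessions. The other is a head count. A referral share of 10–30% would give 34–101 referred women, 17–50 split pairs and up to 34–100 women unblinded. The protocol supports no referral share, and the count needs every referral to have a different referrer, every pair to overlap in time, and every split pair to compare notes and conclude correctly.

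**What to change.** 1. Delete snowballing from the section on identifying participants and from the ethics response, so that both match the three strategies in the Recruitment section.
2. Ask at screening whether the woman knows a current or former participant, and record the link. Acquaintances can also arrive through hospitals, posters or advertisements.
3. State among the procedures against communication that all participants are told not to discuss their sessions with other participants.
4. Add a sensitivity analysis of the primary outcome excluding linked participants, with the full randomised set remaining primary. An enrolled woman becomes linked only after her own randomisation, when someone she knows joins, so this analysis is supportive only.

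The cost is a wording amendment, one screening question and the loss of one minor channel; the three main channels remain. The protocol describes the trial as still preparing to recruit, so the change is cheap at that stage, whereas lost blinding cannot be restored. No waiting-period eligibility criterion is needed: it would restrict entry, yet a woman enrolled later could still hear what her acquaintance had felt.

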**How will formal recruitment of potential participants be conducted?**

This study will use a PROC PLAN software environment (SAS version 9.4, SAS Institute Inc., Cary, NC, USA) for stochastic randomization. A third party produced a confidential dynamic randomization scheme using the Interactive Web Randomization System (Beijing LNKMED Tech Co., Ltd., Beijing, China, http://www.lnkmed.com/edc/a/sysIndex). The group assigned to each participant will be determined by a randomized file. Files will be randomly generated according to statistical units (SAS blocks). When the appropriate district length is selected, a random number of 336 participants will be generated for each of the three centers at a 1:1 ratio (this number shall not be reused) and will include the treatment assignments with corresponding serial numbers: 1001-1336, 2001-23316-336, and 3001-3336 (i. e., random coding table). After screening each eligible participants., the researchers at each center who did not participate in the treatment or evaluation were asked by the research assistant (non-blind personnel) to log into the randomized system and issue the center number randomly according to the enrollment order of the participants . For participants who complete the composition work although do not receive treatment, the random number cannot be reassigned to another participant. The next enrolled participant will receive the next random number in order. To ensure that each participant will receive the same chance of trial conditions in this randomized controlled study, we will balance the influence of confounding factors, avoid trial bias caused by subjective and random arrangements, and provide a scientific basis for statistical analysis. Participants from the three centers who are eligible for enrollment will be randomly assigned to receive an electric or sham needle using a 1:1 ratio. The present study design has been demonstrated as the most effective method for avoiding selection bias. Specifically, after allocation within the LNKMED Interactive Web Randomization System by a research assistant who will not be participating in the treatment and evaluation procedures, basic patient information will be entered into the allocation system to enroll patients meeting the inclusion criteria into the randomization process and obtain the corresponding randomization numbers and groupings. After enrollment, the clinical researcher will record the demographic information, including age, race, marital status, education level, employment status, comorbidities, and body mass index, within the study data system. Moreover, the duration of dysmenorrhea, treatment history, and related scale scores will be recorded before treatment. The study protocol includes regular monitoring and bias evaluations among centers.

The randomization scheme and parameters set during scheme generation are collectively known as the blind background. This study follows a first-level blind design, in which the primary randomized number corresponds to the actual treatment group. The random coding table is generated by the statistical unit, and the blind bottom will be sealed separately and delivered to the responsible clinical trial unit at The First Affiliated Hospital, Department of Chinese Medicine, Hengyang Medical School, University of South China.

The central randomization system designates strict personnel authority. More specifically, no one other than the highest administrator is allowed to view the random scheme within the system, thereby ensuring a completely random distribution and effectively eliminating human interference and error.

The investigator will not perform emergency unblinding unless grouping information is required to medically treat the patient.

In this trial, the emergency unblinding process involves electronic emergency letters. When the investigator believes that the grouping information is required for the treatment of serious adverse events, emergency unblinding can be achieved through the LNKMED Interactive Web Randomization System. Meanwhile, the researcher will record the relevant data in detail, including the time of unblinding, cause, trial treatment, treatment, etc. Once the electronic emergency envelope is opened, the participant will be treated as a shedding case.

**Please provide a response to any ethical issues and concerns raised by the recruitment process such as the relationship between researchers and participants, risks associated with recruitment strategy, and the nature of the population being examined.**

There is no single correct approach, but a balanced recruitment approach will be employed (e.g., use snowballing as well as public advertisement). Recruitment of participants should be viewed as part of the research protocol and should require appropriate informed consent of the already-enrolled participant. Investigators should inform prospective participants why they are being contacted, how information about them was obtained, and what will happen to that information if they decide not to participate.

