**Statistical analysis:**

Descriptive statistics

We will perform statistical analyses using SPSS statistical software (version 26.0, IBM Corp., Armonk, NY, USA). A mixed-effect model will be used to compare change values before and after treatment for continuous variables. This analysis model divides the baseline scores as study covariates, accounting for grouping and central effects. Based on this model and differences before and after treatment, we will calculate the least squares mean of the two groups and the associated 95% credible interval of the difference between the two groups. Fisher's exact parametric method and nonparametric Kruskal Wallis tests will be used to evaluate dichotomous variables. Report exact p-values for all values greater than or equal to 0.001.A two-sided P-value of < 0.05 is considered the threshold for statistical significance.

Metabolomics analysis

We will perform first signal denoising, baseline and phase correction for all spec graphs, piecewise data integration, row and column normalization, and scaling normalization to conduct the metabolomics analysis. All data are to be processed using MestReNova software (Mestrelab Research, Santiago de Compostela, Spain). Pattern recognition analysis includes adopting the principal component analysis method of unsupervised mode recognition as well as a classification analysis (SIMCA), a partial least squares method, and a neural network method. All of these procedures will be conducted using SIMCA-P software (version 14. 0, Umetrics AB, Umea, Sweden). Pearson correlation analysis will be used to analyze characteristic hematuria metabolites as well as to determine the metabolites specific to PDMM and their associated metabolic pathways.

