**Statistical analysis**

For the primary outcome, rates of recruitment (numbers consented/eligible), completion (undertaken baseline and follow-up tests), adherence (participant completed sessions/number of sessions), and adverse events (number and number per participant hour) will be calculated. Secondary outcome will be assessed following intention-to-treat principles. Repeated measures ANOVA will be conducted to assess changes in secondary outcomes throughout the study. This model allows inclusion of missing data in an intention-to-treat analysis without imputations (e.g. last-observation-carried-forward). If necessary, analysis will be adjusted for baseline levels and potential confounding factors. Normality assumptions will be assessed using the Shapiro-Wilk test. Statistical significance will be set at an alpha level of 0.05. Corrections will be applied to all analysed outcomes to account for multiple comparisons.

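### An emergency code break automatically makes the participant an undefined 'shedding case', which can end outcome collection although the participant has not withdrawn

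*Protocol*

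**What the plan says.** The rule stands in the protocol section *How will formal recruitment of potential participants be conducted?*, in the text on emergency unblinding. Unblinding is limited by need: "The investigator will not perform emergency unblinding unless grouping information is required to medically treat the patient". The route is then described: "When the investigator believes that the grouping information is required for the treatment of serious adverse events, emergency unblinding can be achieved" through the web randomisation system, with time, cause and treatment recorded. The consequence follows at once: "Once the electronic emergency envelope is opened, the participant will be treated as a shedding case". The protocol defines this status nowhere and gives no exception.

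Three other places bear on it:

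- The second *Statistical analysis* section (after the data-collection text) states: "Secondary outcome will be assessed following intention-to-treat principles". Of its repeated-measures model it says: "This model allows inclusion of missing data in an intention-to-treat analysis without imputations (e.g. last-observation-carried-forward".
- The first *Statistical analysis* section, which covers continuous variables such as VAS, says: "A mixed-effect model will be used to compare change values before and after treatment for continuous variables". It names no analysis set.
- *Risk – Physical Risks* requires every identified adverse event to be followed until it resolves or is judged permanent, and makes no exception for unblinded participants.

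**The concern.** The natural reading of *shedding case* is dropout. If so, the investigator's need to know the allocation turns a participant into a dropout, although she has neither withdrawn consent nor missed a visit. *Data collection method and location* treats withdrawal as the participant's own free decision; the unblinding rule adds an automatic one.

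The trigger is a serious adverse event after randomisation, so the status depends on a safety outcome and may depend on arm. If sites apply the label in the usual way, scheduled VAS and questionnaire assessments may stop, and new adverse events may go unrecorded. *PICOs* plans 12 weeks of treatment and 12 weeks of follow-up, so an early code break could cost most of a participant's outcome data. A later analysis plan can define who is analysed, but it cannot recover scores that were never taken.

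**Working it through.** **The passages side by side**

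1. *Trigger.* The allocation is needed to treat a serious adverse event. This is a post-randomisation event.
2. *Consequence.* The participant becomes a shedding case. The text says neither that scheduled assessments continue nor that they stop. Three centres could therefore handle the same event differently.
3. *Intention-to-treat.* The principle is stated for the secondary outcome. It calls for analysis as randomised and, in good practice, for continued outcome collection. A dropout can still be analysed as randomised on the data observed, and the protocol says its model accepts missing data. The rule therefore works against the principle by creating gaps, but does not by itself break it.
4. *Outcomes touched.* The second *Statistical analysis* section begins: "For the primary outcome, rates of recruitment (numbers consented/eligible), completion (undertaken baseline and follow-up tests), adherence", and it adds adverse events per participant hour. Automatic dropout lowers completion directly and can shorten the time over which new events are recorded.
5. *Safety.* The triggering event precedes the code break and is followed to resolution under *Risk – Physical Risks*. Only later, new events are exposed.

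**Scale**

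The protocol gives 168 per group and a two-sided 0.05 threshold. It gives no effect size, SD, power, dropout rate or code-break rate, so its sample size cannot be reproduced and everything below rests on assumptions.

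*Shift in one arm's mean VAS change.* Assume that k of 168 participants are lost, that they have no change, and that the rest fall by 3 cm on average. The shift is 3 × k/168:

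- k = 2: 3 × 2/168 = 0.036 cm
- k = 5: 3 × 5/168 = 0.089 cm
- k = 8: 3 × 8/168 = 0.143 cm

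*The same in SD units.* If a share f of an arm is lost and its mean differs by g SD from the rest, the arm's mean shifts by f × g:

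- f = 0.5%, g = 0.5: 0.005 × 0.5 = 0.0025 SD
- f = 5%, g = 1: 0.05 × 1 = 0.05 SD

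Both are shifts in a single arm. The comparison between arms is biased only to the extent that the shifts differ.

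*Power.* With 168 per arm, the detectable standardised difference is d = (z for 0.975 + z for power) × √(2/168):

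- 80% power (assumed): (1.960 + 0.842) × 0.1091 = 0.306
- 90% power (assumed): (1.960 + 1.282) × 0.1091 = 0.354

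Losing 0.5% to 5% of each arm removes about 1 to 8 participants (168 × 0.005 = 0.8; 168 × 0.05 = 8.4). Holding d fixed, power falls from 80.0% to between 79.8% and 78.0%, or from 90.0% to between 89.9% and 88.5%. Lost power is not the issue; any harm would come from loss that is related to outcome and uneven between arms.

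**The case against.** The best defence is that the sentence assigns a label and no more. Several stronger readings are tempting, and the document does not support them.

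- *Randomised participants are removed from the analysis.* A reader might infer this, but nothing in the protocol excludes shedding cases from an analysis set, discards their data or cancels their visits. Analysis sets may also be defined in an analysis plan that is not at hand. This objection stands.
- *The rule contradicts intention-to-treat.* This is not shown. The principle is stated only for the secondary outcome, in a section that names feasibility rates as the primary outcome. The section covering VAS names no analysis set, so no intention-to-treat promise for VAS can be cited as broken. This objection also stands.
- *Serious events are lost from the safety data.* They are not: the triggering event is already recorded and must be followed to its end.
- *The bias favours one arm.* The protocol does not link serious events to pain response, and gives no rate by arm. Direction is unknown.

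A last objection is that the matter can wait for the analysis plan. That holds for analysis sets and sensitivity analyses. It does not hold for whether visits continue, which this sentence governs, however loosely, and which sites must act on at the time.

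Nor does blinding justify the rule. Opening the code informs the investigator, but need not inform the participant who rates her own pain.

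**Conclusion.** The point holds in a limited form. The protocol imposes an undefined status, most naturally dropout, on every emergency-unblinded participant because of a post-randomisation safety event and without any withdrawal on her part. Applied as written, it can end collection of VAS, other outcomes and new adverse events. The resulting missing data would be avoidable and possibly informative, and the rule sits poorly with the intention-to-treat principle stated for the secondary outcome.

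The effect is probably small: at most about 0.14 cm in one arm's mean on a 10 cm scale, or about 2 points of power, under the assumptions above. These rest on assumed counts, an assumed 3 cm fall and no usable data from those lost; code breaks may be rarer. The reading of the undefined term is itself an assumption, though the natural one. The sentence should be changed because it fixes a poor rule that is cheap to replace, not because it threatens the trial's result.

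**What to change.** Replace the sentence with wording such as: *A code break is recorded with its time and reason. It does not by itself end scheduled outcome and safety data collection, which continues unless the participant withdraws consent. The participant is analysed in the randomised group.* Leave decisions on continuing or stopping treatment as they are. If the term shedding case is kept elsewhere, define it.

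A sensitivity analysis without scores taken after unblinding is optional and can be left to the analysis plan.

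The cost is one sentence and visits already scheduled. The protocol describes the study as preparing for recruitment, so on that footing the change can be made before any data are lost. The small downside is that some scores will come from participants who may know their allocation; the recorded time of each code break allows these to be identified.
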